#### Adverse event management

Mortality rate is closely monitored. If the mortality rate becomes 50% higher for the intervention group the trial steering committee will be asked to evaluate individual case notes, reports and general aspects. The trial will be closed if the difference holds a significance level p < 0.10.

### Power and statistical analyses

Sample size estimates are based on mobility assessed by SPPB at 4 months following the fracture. A change in the SPPB score of 0.5 points is considered a small but meaningful change, while 1 point is considered a more substantial change. In order to detect an effect size of 1.0 when power is 80% and alpha = 0.05, a sample size of 304 participants would be needed. Based on data from a previous prospective observational study in a similar study population (work in progress), we expect a drop out rate of 10% due to death and 10% due to withdrawals during the first 4 months following the fracture. To allow for 304 patients to remain in the project at four months after the fracture 380 persons need to be included. Thus, the plan is to include a total sample of 400 participants. The assumptions underlying the sample size (i.e. the standard deviation at baseline) has been checked by an independent clinical trials unit after the first 200 patients enrolled, and found to be acceptable.

All data will be analysed and presented according to the updated CONSORT guidelines for reporting parallel group trials[60]. Patterns of missing data will be explored prior to analysis, and accounted for in the analysis by imputation methods [61]. To study differences in change between groups we will use multivariate analyses by use of mixed models for longitudinal data by general linear modelling (GLM) for continuous outcomes and by logistic regression for binary outcomes [62]. To study associations between the new clinical pathway and time to events, we will use Kaplan Meyer plots and the Cox proportional hazards regression model. In all analyses we will control for confounding factors and interactions and present both unadjusted and adjusted effects with 95% confidence intervals.

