**Methods/design:**

The intervention of interest, a comprehensive geriatric assessment is compared with traditional care in an orthopaedic ward. The study includes 401 home-dwelling older persons >70 years of age, previously able to walk 10 meters and now treated for hip fracture at St. Olav Hospital, Trondheim, Norway. The participants are enrolled and randomised during the stay in the Emergency Department. Primary outcome measure is mobility measured by the Short Physical Performance Battery (SPPB) at 4 months after surgery. Secondary outcomes measured at 1, 4 and 12 months postoperatively are place of residence, activities of daily living, balance and gait, falls and fear of falling, quality of life and depressive symptoms, as well as use of health care resources and survival.

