### Aims

#### Primary aim

• To estimate the effect on mobility 4 months after surgery of treating hip fracture patients in an orthogeriatric ward as compared to treatment in an orthopaedic ward.

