### Intervention

Patients randomised to the intervention group are transferred directly from the Emergency Department to the orthogeriatric ward while control patients are transferred to the trauma unit at Department of Orthopaedic Surgery. Orthopaedic surgeons are responsible for the initial assessment, diagnosing of the fracture and decisions on type of surgery for both groups. Anaesthesiologists make preoperative assessments regarding analgesia, operability and perioperative anaesthesiological procedures. After surgery and for a limited time period all patients are observed in the recovery unit.

On request orthopaedic surgeons examine study patients in the orthogeriatric ward and supervise the staff. Geriatricians serve the orthopaedic ward equivalently.

The experimental intervention program is offered only during the acute hospital stay. The orthopaedic surgeons decide on traditional follow-up consultations after discharge irrespective of group allocation.

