#### Experimental group

Physicians at the Department of Geriatrics or residents on call have the 24-hour medical responsibility pre- and postoperatively.

The treatment strategy is based upon CGA which is a systematic and multidimensional diagnostic process focusing on evaluation of frail elderly persons' medical, psychosocial and functional capabilities and limitations in order to develop a coordinated and integrated plan for treatment and long-term follow-up by the primary health care system [25]. An interdisciplinary team consisting of geriatricians and residents, nurses, physiotherapists and occupational therapists with special competence in geriatrics is responsible for the CGA program. The team emphasizes adequate nutrition, early mobilization and functioning in activities of daily living, initial in-hospital rehabilitation and early discharge planning. Discharge planning starts as early as possible involving all team members. Whenever possible, patients are recommended to receive post discharge rehabilitation in their own home. In addition to treatment of current medical conditions, the management program also focuses on factors related to the fall incident causing the fracture.

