#### Data collection

For practical reasons it is not possible to implement systematic blinding of testing during the hospital stay. For the 1-, 4-, and 12-month assessments testers will not have access to information about the patients' group assignment.

Background information on living conditions, physical and cognitive function before the fracture is collected for all participants starting already during the stay in the Emergency Department. On day 3 or 5 research assistants collect details from patients' on falls history, use of mobility aids, pre-fracture scoring of Barthel ADL-Index and Nottingham extended I-ADL Scale when the clinical condition makes it appropriate, or from proxies when they are available. These registrations will be used as explanatory variables in the statistical analyses.

Mobilisation is monitored using CAS during the 3 first days after the operation. On day 3 a research assistant attaches an ActivPal sensor anteriorly on the non-affected thigh for at least a 24-hour activity monitoring. The sensor is removed on day 5. On day 5 or the nearest working day a SPPB mobility score is completed by a research assistant.

Research assistants will continually scrutinise study forms on missing data. Missing data from proxies are collected through telephone calls, as is also information needed to fill in the CDR form. Electronic hospital records will give further information on clinical examinations, medication, blood tests and other investigations performed during the index stay.

The 1-month registration is performed by research assistants at the site where the patient is living, irrespective of location. This might be the patient's own home, a nursing facility or a rehabilitation institution. The time window is 4 weeks ± 5 days. For details on data collection and questionnaires, see Table 1. Information on Barthel ADL Index or Nottingham extended I-ADL Scale items are collected primarily from the patients depending of cognitive function, or alternatively from the proxy. Whenever possible, information on participants living at remote locations from St. Olav Hospital is collected by trained local physiotherapists hired as research assistants.

**Table 1 T1:** Measures, scales, questionnaires and time-points of data collection

Index stay	1 month postoperatively	4 and 12 months postoperatively
CAS (3 days)		
SPPB	SPPB	SPPB
TUG	TUG	TUG
	Place of residence	Place of residence
	MMSE	MMSE
	GDS-15	GDS-15
	FES-I	FES-I
	EQ-5D	EQ-5D

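### The stated analysis targets change between groups, but the primary endpoint is SPPB level at 4 months and no SPPB precedes treatment; any early effect would be subtracted if the change contrast were applied to SPPB

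*Protocol article*

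**What the plan says.** **Target.** The abstract (Methods/design) states: "Primary outcome measure is mobility measured by the Short Physical Performance Battery (SPPB) at 4 months after surgery". The primary aim is "To estimate the effect on mobility 4 months after surgery of treating hip fracture patients in an orthogeriatric ward", compared with an orthopaedic ward. The section Power and statistical analyses bases the sample size on SPPB at 4 months, with 304 evaluable patients for an effect of 1.0 at 80% power and alpha 0.05.

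**Analysis.** The same section gives one sentence for continuous outcomes: "To study differences in change between groups we will use multivariate analyses by use of mixed models for longitudinal data". It does not name the reference time for change, and it does not say which model contrast is the primary test. It also promises control for confounding factors in all analyses, with unadjusted and adjusted effects both presented.

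**First SPPB.** Under Data collection: "On day 5 or the nearest working day a SPPB mobility score is completed by a research assistant". Table 1 lists SPPB at the index stay and at 1, 4 and 12 months. Its block of pre-fracture measures holds Barthel, Nottingham I-ADL, falls, walking aids and CDR, but not SPPB. The same section says that testing in hospital cannot be systematically blinded.

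**Start of treatment difference.** Under Intervention: "Patients randomised to the intervention group are transferred directly from the Emergency Department to the orthogeriatric ward". In the experimental group the geriatric physicians or residents on call "have the 24-hour medical responsibility pre- and postoperatively", and "The team emphasizes adequate nutrition, early mobilization and functioning in activities of daily living". Also: "The experimental intervention program is offered only during the acute hospital stay".

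**The concern.** A comparison of levels at 4 months and a comparison of changes up to 4 months estimate the same effect only when the arms are expected to be equal at the starting point. Randomisation ensures that for a measurement taken before allocation. It does not for a score taken on day 5, during a programme that promotes early mobilisation. Such a score is an early outcome.

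If it, or the 1-month score, is the starting point for change, an early gain that lasts to 4 months cancels out of the comparison. The trial could then report little or no effect because the intervention worked early and the benefit held. The quantity tested would also not be the one for which 304 patients were planned. The sample-size paragraph's mention of a standard deviation at baseline makes it plausible, though it is not stated, that the in-hospital score is regarded as a baseline.

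**Working it through.** **1. The plan's own figure.** No SD is given, so 304 can only be solved backwards, assuming a two-sided test and 1:1 allocation:

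SD = 1.0 × √(152/2) / (1.960 + 0.842) = 8.718 / 2.802 = 3.11 points.

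Putting 3.11 back in returns 152 per arm, 304 in all. Read as a standardised effect, 1.0 would need only 32 patients, so it must mean one SPPB point. The dropout step reproduces exactly: 304 / 0.80 = 380.

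**2. The two contrasts.** Let D4 be the true between-arm difference at 4 months and D5 the difference on day 5.

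- Level contrast: D4, with standard error 3.11 × √(2/152) = 0.357. For D4 = 1.0, power is 80% whatever D5 is.
- Change contrast from day 5: D4 − D5. With equal SDs at both visits and within-person correlation ρ, the SD of change is 3.11 × √(2(1 − ρ)), which is 3.68, 3.11 and 2.41 for ρ = 0.3, 0.5 and 0.7.

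**3. Results for D4 = 1.0 and 152 per arm.** D5 and ρ are assumptions; the documents give neither.

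| Assumed day-5 benefit | Expected change estimate | Power, ρ = 0.3 | Power, ρ = 0.5 | Power, ρ = 0.7 |
|---|---|---|---|---|
| 0 | 1.00 | 66% | 80% | 95% |
| 0.25 | 0.75 | 42% | 55% | 77% |
| 0.5 | 0.50 | 22% | 29% | 44% |

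For scale, the protocol calls 0.5 points small but meaningful. A simulation of 4,000 trials at ρ = 0.5 and a day-5 benefit of 0.5 gave a mean level contrast of 1.02 with 81% power, and a mean change contrast of 0.51 with 31% power. With a day-5 benefit of 1.0, the change contrast averaged 0.00 and was rejected 5% of the time.

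**4. Day-5 SPPB as a covariate.** Adjustment would remove about ρ × D5 instead of all of D5. At D5 = 0.5 the estimate becomes 0.85, 0.75 or 0.65 for ρ = 0.3, 0.5 or 0.7.

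**5. A different reference visit.** Starting from 1 month does not help. That visit is also after randomisation, and any effect present then would be subtracted in the same way.

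**The case against.** The analysis sentence is generic. It covers all continuous and binary outcomes and does not mention SPPB. Change is a proper target elsewhere: one secondary aim concerns change in gait control and daily physical activity over a year. The 4-month endpoint is stated clearly in several places, and a longitudinal mixed model can deliver the 4-month between-arm difference. This is a condensed article, and the reference visit, the primary contrast and the covariate list are commonly left to the SAP.

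Much of this stands. The model class is not at fault, and the absence of such detail is not the point. What remains is that the one contrast the article does name conflicts with its own endpoint, and would give a biased answer if applied to SPPB.

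Four stronger readings are tempting but not supported:

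- *Day-5 SPPB is the declared baseline and will be subtracted.* No sentence says so.
- *Day-5 SPPB will be adjusted for.* The explanatory variables named under Data collection describe the time before the fracture, and SPPB is not among them. The promise to control for confounding is not limited to such variables, but it does not name SPPB either.
- *Power will fall to a particular figure.* The loss depends on an assumed early benefit and an assumed correlation. At ρ = 0.7 a 0.25-point early benefit still leaves 77% power. With no early benefit the change estimate is unbiased, and its power may be below or above 80%.
- *The timing of the day-5 test differs by arm.* The text gives only day 5 or the nearest working day, and documents no difference between arms.

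**Conclusion.** The concern holds as a conflict between the stated contrast and the plan's own primary endpoint. The subtraction itself is algebra: any SPPB change contrast in this trial removes whatever difference exists at its starting visit, because every SPPB follows allocation. That day 5 is the intended reference is an inference, as is counting it from surgery, which the text suggests by the preceding sentence on the first three days after the operation.

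The size is conditional. With a two-sided test, SD 3.11, 152 per arm, equal SDs over time and a true 4-month difference of 1.0, an early benefit of 0.5 halves the estimate and leaves 22% to 44% power over correlations of 0.3 to 0.7. A benefit of 0.25 leaves 42% to 77%. The level contrast keeps 80% throughout. The point deserves correction before analysis because it concerns the primary test and the bias runs against an intervention that works early.

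**What to change.** State in the analysis section or SAP:

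1. The primary test is the between-arm difference in mean SPPB at 4 months, estimated as the 4-month contrast from the mixed model with the day-5, 1-, 4- and 12-month scores all as outcomes.
2. Day-5 SPPB is neither subtracted nor adjusted for. The same applies to other in-hospital measures taken after randomisation, such as TUG, CAS and ActivPal.
3. Adjustment is limited to variables describing status before randomisation or before the fracture, such as age, sex, fracture type, and pre-fracture Barthel and Nottingham I-ADL. The last two need a caveat: they describe the time before the fracture but are collected on day 3 or 5, after allocation and without blinding. The unadjusted effect, already planned, should therefore stand beside the adjusted one.
4. Group-by-time comparisons of change are secondary.
5. The reference to a baseline SD names the visit and measure it comes from.

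The cost is a few sentences. No new data are needed, and 304 evaluable and 380 enrolled are unchanged. The Discussion says that analysis had not begun when the article was written, so the wording could be settled before the 4-month database is finalised.

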### Time plan of the study

Since study start on April 18^th ^2008 until December 30^th ^2010 altogether 1077 hip fracture patients have been admitted to the Emergency Department at St. Olav Hospital, Trondheim University Hospital and screened for eligibility, of whom 401 have consented to participation, see Figure 1.

**Figure 1 F1:**
[figure not shown]
**Flowchart**. Overview of patients and attrition rates at enrollment, index stay and follow-up 1, 4 and 12 months after the hip fracture. Attrition rates at all assessment time points are presented as estimated percentages of participants allocated into the study (%). The estimates are based on preliminary data from an observational study in our department.

The final 12-month registrations will take place in December 2011. The formal analyses are estimated to start when the data base on the 4-month primary endpoint measures of mobility is finalised by May 2011. With exception of the study statistician, the study team will be masked from the trial results until the final follow up is completed.

#### Ethics and approvals

The study is approved by the Regional Committee of Ethics in Medical Research (Mid-Norway) (REK4.2008.335), the Norwegian Social Science Data Services (NSD19109), and the Norwegian Directorate of Health (08/5814).

## Discussion

Presenting this paper of the study protocol covering design, outcome measures, power calculations and procedures of the Trondheim Hip Fracture Trial is in accordance with general guidelines for reporting of RCT protocols for complex interventions [24], although it is published after the conclusion of the recruitment phase but still before the onset of data analysis and while the data collection is going on.

The objective of the study is to evaluate the impact of CGA on older hip fracture patients still having potential of functional improvement and preservation of health related quality of life aiming at prolonging their ability to live in their own home. Excluded are young hip fracture patients, patients with terminal illness, permanent nursing home residents and patients unable to walk. Patients with cognitive impairment and also temporary nursing home residents are included, representing patients known to be at especially high risk of further deterioration. Therefore, the study sample should comprise the most relevant segments of hip fracture patients regarding measurable benefits of CGA, being neither too healthy nor too ill.

We have chosen mobility as the primary endpoint, mainly because impaired mobility is one of the most feared consequences of a hip fracture in addition to death and nursing home placement, hopefully being accessible for intervention [16]. Still, potential benefits of CGA on mobility at 4 months will be more or less an indirect consequence of the intervention. Although mobility has been defined as the most important outcome, several secondary study outcomes i.e. ADL and I-ADL, health related quality of life, the extent of being discharged to own home, and costs may be equally relevant. This study is not sampled for mortality and nursing home placement as endpoint, and thus this information will only be used for hypothesis generation for future studies.

The context and organisation of care pathways for hip fracture patients differ extensively even in a small country like Norway. Nevertheless, there are consistent efforts by hospital managements towards shortening of hospital LOS based on fast-track orthopaedic services. Important consequences are less time for stabilisation of clinical conditions, assessment and treatment of relevant co-morbidity, as well as shifting of rehabilitation services out of hospitals, contrasting important constitutive elements of CGA-based specialist services.

Since the present intervention program will not implement any kind of medically follow-up by geriatric specialist services, and recommendations are to be dealt with by general practitioners and nursing homes or rehabilitation facilities outside hospital, important aspects of CGA may be lost. However, the competence and compliance of primary health care system vary extensively. Limitations of the study might thus be related both to study sample, non-blinding of assessors and choice of endpoints, as well as content and performance of the experimental intervention program.

The most important challenge is still the black box of inter-linked elements of CGA, of which we still do not know what is actually working. Therefore, evaluating the benefit of CGA within the present context without including an extended and optimal geriatric rehabilitation service or a relevant follow-up program after discharge from hospital may in fact increase the knowledge base as to the most important elements of CGA. The present study will hopefully be able to designate potential predictors of a successful or non-successful care pathway.

To our knowledge the present study is the largest and most comprehensive RCT investigating CGA on elderly persons having suffered a hip fracture. There is however need of more research on alternative care pathways [16]. As a second step our research group is now implementing two studies. The first one will focus on potential benefits of a more extensive involvement of and follow-up by the community care system including physiotherapy in the patient's own home to start immediately after discharge from hospital or after returning home from an out-of-hospital rehabilitation facility. This is a case-control study with historic controls from the present study. The second study is a RCT investigating the potential effect of a boost of a 10 weeks intensive physiotherapy program 4 months after the hip fracture.

In conclusion we believe that study design, randomisation procedure and outcome measurements will be of sufficient strength and quality to evaluate important impacts of CGA during the index stay on mobility and other relevant outcomes in hip fracture patients.
